## Introduction

### Background and rationale {6a}

#### The interaction of pain and emotional well-being

Pain is a psychophysiological warning sign that protects us from potential danger [36]. However, pain, especially when it manifests as a chronic condition, may become a profound problem for the affected individual. Worldwide, chronic pain is among the most common causes for seeking medical care, with a global prevalence of 15% to 45% and estimated economic costs in the US at $600 billion annually [49, 54]. Research findings highlight the negative effects of chronic pain on quality of life [10] in both private and professional life [16]. Considering these findings, it is not surprising that up to 75% of chronic pain patients experience comorbid depressive symptoms [32].

The relationship between chronic pain and depressive symptoms is likely bidirectional. On the one hand, depression can contribute to the multifactorial genesis of chronic pain [47], while on the other hand depressive symptoms can emerge as a result of impairments in psychosocial functioning and low quality of life due to chronic pain [44].

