### Sample size {14}

The sample size calculation was conducted using G*Power®. Given that Miegel and colleagues [39] examining the effect of an unguided Internet-based interventions for depression on chronic pain patients found small to moderate effects, a moderate effect in the current study can be expected [39]. For analysis of covariance, the software yielded a required sample size of 246 with an expected effect size of η_p_^2^ = 0.06 (moderate effect), an alpha of 0.05 (two-sided), and a power of 0.95. We expect a drop-out rate of 25%. Hence, we aim to recruit 300 participants in total, with 100 participants per condition.

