### Eligibility criteria {10}

For inclusion in the RCT, participants must meet the following criteria:Presence of depressive symptoms (Beck Depression Inventory-II (BDI-II) score ≥ 14; Patient Health Questionnaire-9 (PHQ-9) score ≥ 10),Chronic pain symptoms (mean score pain intensity on the German Pain Questionnaire (DSF) ≥ 4),Aged 18 to 75 years,Informed consent,Sufficient knowledge of the German language,Willingness to participate in three anonymous online surveys,Willingness to use the Internet-based treatment program over a period of 8 weeks minimum, andAccess to a computer/laptop and a smartphone.

The program has been developed for a heterogeneous target group of chronic pain patients with comorbid depressive symptoms. No formal diagnosis (of chronic pain and/or depressive symptoms) is needed as symptoms will be assessed by validated questionnaires at baseline. Effects of prior diagnoses as well as concurrent treatment programs will be analyzed in moderation analyses (see statistical analyses).

Exclusion criteria are a lifetime diagnosis of a schizophrenia spectrum disorder, bipolar disorder, substance abuse disorder, or acute suicidality (assessed by one item on suicidality on the Web Screening Questionnaire; WSQ).

Inclusion and exclusion criteria will be assessed at baseline. Excluded participants will be forwarded to an additional survey page providing the reason for exclusion and a contact e-mail address of the principal study investigator. In case of exclusion due to acute suicidality, participants will also be provided with phone numbers of crisis services.

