### Outcomes {12}

The primary outcome will be pain impairment (mean value of impairment in daily life, free time, work) as assessed by the DSF (German pain questionnaire). The DSF is a commonly used, reliable, and validated instrument for the assessment of chronic pain [9]. We decided on pain impairment as the main outcome as Lenio especially targets the psychological aspects of chronic pain. Hence, we expect a significant improvement in different aspects of life, including daily life, leasure time, and work. The secondary outcomes will include depressive symptoms as well as the severity of pain symptoms. Furthermore, subjective evaluation and possible side effects will be assessed.

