##### University of Rhode Island Change Assessment Scale (URICA)

The URICA is a self-report questionnaire developed to assess various stages of change in complex problem behavior [35].The URICA has demonstrated high internal consistency, with a Cronbach’s α of 0.77 to 0.82 and good reliability [15]. It predicts both treatment success as well as drop-out rates [35]. The present study will use the German version of the URICA (Fragebogen zur Erfassung der Veränderungsbereitschaf, FEVER, [19]). The FEVER captures three different phases of change: (1) pre-contemplation, i.e., lack of readiness to engage in an intervention or no readiness to change, (2) contemplation, i.e., readiness to engage in an intervention or to change something, and (3) action, i.e., the decision to change something and the use of active strategies to change. For the current study, a shorter version with only three items per phase (total of nine items) will be used. The FEVER/URICA will be assessed at baseline only. The subscales “precontemplation,” “contemplation,” “preparation,” “action,” and maintenance” will be calculated.

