## Statistical methods

### Statistical methods for primary and secondary outcomes {20a}

All analyses will be conducted using IBM SPSS Statistics® 27. The data will be exported from Qualtrics® into SPSS® and initially stored on a secure server and later a password-protected computer. The security of data transmission via the Internet is also guaranteed by SSL encryption. Data will be analyzed using analysis of covariance (ANCOVAs), with between-group differences over time (pre-intervention to post-intervention) as the within-group factor and different conditions as the between-group factor. Baseline scores will serve as covariates, group allocation as the independent variable, and post- and follow-up scores of primary and secondary measures as dependent variables. Group differences at baseline will be assessed using independent t-tests for continuous variables. Partial eta square will be calculated as effect size.

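### The primary ANCOVA is valid but names only baseline scores as covariates; adding baseline pain intensity and BDI-II would be a cheap improvement of unknown, possibly nil, size

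*Protocol article*

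**What the plan says.** Protocol article, Statistical methods {20a}: "Baseline scores will serve as covariates, group allocation as the independent variable", with "post- and follow-up scores of primary and secondary measures as dependent variables". No other covariate is named. The sections on trial design and participant timeline mention no stratification factor that the model would have to carry.

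Outcomes {12}: "The primary outcome will be pain impairment (mean value of impairment in daily life, free time, work) as assessed by the DSF".

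Sample size {14}: a "required sample size of 246 with an expected effect size" of partial eta squared 0.06, "an alpha of 0.05 (two-sided), and a power of 0.95", 25% expected drop-out and a target of 300.

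Baseline information available for other uses:
- Eligibility {10} requires "mean score pain intensity on the German Pain Questionnaire (DSF) ≥ 4" and minimum BDI-II and PHQ-9 scores, so all three are recorded for everyone randomised.
- The background section states: "The relationship between chronic pain and depressive symptoms is likely bidirectional".
- The URICA section, on a scale given at baseline only, states: "It predicts both treatment success as well as drop-out rates".

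Section {20b} considers all baseline variables as potential moderators, on an exploratory footing. Section {20c} plans multiple imputation for the intention-to-treat analysis and does not list the imputation variables.

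**The concern.** A baseline variable that predicts the outcome beyond the outcome's own baseline removes residual variance when it is in the model, and so narrows the interval for the treatment effect without further participants. Here the candidates are already collected, and the article itself links depression to pain and readiness to change to treatment success. If they predict pain impairment at week 8, leaving them out of the primary model gives up some precision.

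The point has some practical weight because recruitment is reported as completed. Numbers can no longer be raised, and 25% drop-out from 300 leaves 225 completers, fewer than the 246 that the calculation asks for.

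Drop-out is a separate matter. A variable that predicts who leaves does not for that reason make the ANCOVA more precise. Its natural place is the imputation model, where it makes the missing-at-random assumption easier to defend.

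**Working it through.** **Inputs from the article.** Three arms at 1:1:1, partial eta squared 0.06, alpha 0.05, power 0.95, N = 246, drop-out 25%, target 300.

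**Assumed input.** R2 is the share of the variance remaining after own-baseline adjustment that the added covariates explain. The documents do not give it. The range used is 0 to 0.10. The article's effect size is taken to refer to the own-baseline-adjusted model, which it does not state.

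**Step 1: reproduce the stated sample size.**
- f² = 0.06 / (1 − 0.06) = 0.0638.
- Power comes from the noncentral F distribution with λ = f² × N, df1 = 2 and df2 = N − 3 − (number of covariates).
- With one covariate at N = 246: λ = 15.70, df2 = 242, power 0.951.
- The smallest N reaching 0.95 is 245, which becomes 246 for equal arms of 82. The stated figure is reproduced.

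**Step 2: cost if the added covariates are useless.** With three covariates instead of one and R2 = 0, power at N = 246 is 0.9508 in both cases (a change below 0.0001). The required N goes from 245 to 246.

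**Step 3: gain if they explain something.** Residual variance is multiplied by (1 − R2), so f² becomes 0.0638 / (1 − R2) and the standard error is multiplied by √(1 − R2). The equivalent gain in participants is 1/(1 − R2) − 1. Completers are 300 × 0.75 = 225. The table uses three covariates in all.

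| Assumed R2 | SE ratio | Equivalent gain in N | N for power 0.95 | Power at 246 | Power at 225 |
|---|---|---|---|---|---|
| 0 | 1.000 | 0% | 246 | 0.951 | 0.931 |
| 0.02 | 0.990 | 2.0% | 241 | 0.955 | 0.936 |
| 0.05 | 0.975 | 5.3% | 233 | 0.960 | 0.943 |
| 0.10 | 0.949 | 11.1% | 221 | 0.969 | 0.954 |

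**Step 4: what would bring 225 completers back to 0.95.** Approximately R2 = 1 − 225/245 = 0.08. Whether the added covariates reach that cannot be judged from the documents.

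**The case against.** The strongest case against is that nothing here is wrong. Own-baseline ANCOVA is a standard, valid analysis and matches the sample size calculation. A condensed article may leave a fuller covariate list to the full protocol or analysis plan. That stands, and the point is made only as an improvement.

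A reader might infer more than the documents support:
- **That the plan adjusts for the own baseline and nothing else.** Section {20a} says neither own nor only. It is the natural reading, but still an inference.
- **That precision is being lost.** No figure in the article shows that any candidate predicts week-8 impairment once baseline impairment is known. The background statement on pain and depression concerns how each arises. Entry cut-offs on both scores also narrow their range, which tends to weaken prediction. The gain could be close to nil.
- **That the URICA belongs in the primary model.** Predicting treatment success may mean response among treated patients, or effect modification, rather than prognosis in a sample of which one third is on a waitlist. Moderation analysis is a coherent place for it. The trial also uses a shortened nine-item German form, and nothing singles out one phase score as the predictive one.
- **That drop-out prediction is a reason to change the ANCOVA.** It bears on imputation, and nothing shows that the URICA is excluded there.

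Timing also counts. First data were analysed for a March 2022 interim report, and recruitment is completed. A change of primary model now invites questions about flexibility unless it is dated, justified and made before final outcomes are seen.

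What survives is an asymmetry: even useless covariates cost practically nothing, while useful ones would add some precision.

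**Conclusion.** The planned analysis is sound. Naming two further baseline covariates that every participant already has is a low-cost improvement with an uncertain benefit. Under an assumed R2 of 0 to 0.10, the gain in power is between nothing and about 0.018 at N = 246 (0.969 − 0.951), and between nothing and about 0.023 at 225 completers (0.954 − 0.931). These figures rest on the assumed R2, on reading the effect size as own-baseline-adjusted, and on treating 225 completers as the effective sample. The documents do not support calling this an error, a bias or a demonstrated loss of precision. Priority is low.

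**What to change.** In a dated amendment, before final outcomes are examined:

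1. In {20a}, state that the primary ANCOVA of post-intervention pain impairment adjusts for baseline pain impairment, baseline DSF pain intensity and baseline BDI-II sum score. Keep the model with baseline pain impairment alone as a sensitivity analysis.
2. In {20c}, state that the multiple imputation model includes these variables and the URICA/FEVER scores. Use the same analysis covariates in every imputed data set.
3. Record in the amendment that data were analysed for the March 2022 interim report, and that the covariates were not chosen from trial results or from the planned baseline t-tests.

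Cost: two further degrees of freedom in the primary model, one sensitivity run, a few sentences, and a late but documented change to the published model. No new data are needed.

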### Interim analyses {21b}

For the current trial, an interim report has been written on 03/31/2022.

### Methods for additional analyses (e.g., subgroup analyses) {20b}

Explorative moderation analysis will be conducted using the SPSS® macro PROCESS [20] to identify potential moderators for treatment success (all types of baseline variables are being considered in this type of analysis). Furthermore, subjective evaluation of the intervention will be done descriptively by presenting the frequency of positive ratings as well as means and standard deviations.

### Methods in analysis to handle protocol non-adherence and any statistical methods to handle missing data {20c}

Analyses will be conducted for both the intention-to-treat (ITT) and the per-protocol (PP) sample. The PP sample will include only those participants who completed the post-assessment and used Lenio and COGITO at least once. Missing values in the ITT analyses will be estimated using the multiple imputation procedure.

### Plans to give access to the full protocol, participant-level data, and statistical code {31c}

Full protocol, dataset, and statistical codes will be provided upon request.

### Data monitoring and auditing {21a; 23}

An interim report was prepared for the DGUV, who are funding the project, in March 2022. First data was analyzed for this purpose.

### Ethical aspects and data safety

The study will be conducted in accordance with the Guidelines for Assuring Good Scientific Practice and the Principles and Responsibilities for the Conduct of Clinical Trials of the German Research Foundation (DFG). An ethics vote in support of the project has been obtained from the Local Psychological Ethics Committee of the Center of Psychosocial Medicine at the University Medical Center Hamburg-Eppendorf (LPEK-0078a). The study will be conducted in accordance with the Declaration of Helsinki. Any adverse events will be documented and reported {22}. Participants must sign informed consent prior to study participation, which informs them about the study procedure, data protection risks and compensation, and their right to withdraw from participation at any time without giving a reason. If they withdraw, all their data will be deleted.

The research project will be carried out in accordance with the EU General Data Protection Regulation. All other data will be stored on password-protected computers. Data collection will be conducted online using the survey software Qualtrics®, which guarantees high data protection standards such as end-to-end encryption. After completion of the study, the collected data will be archived for 10 years (e-mail addresses will be deleted after the end of the study). The clinical principal investigator (PI) will be responsible to carry out the study in accordance with the study protocol {5d}. The PI will ensure that everyone working in the research project is sufficiently qualified.

### Current study status

Trial start date: November 8th 2021 (first participant was enrolled).

Recruitment is completed.

## Discussion

Lenio is a novel Internet-based self-help intervention addressing symptoms of both chronic pain and depression. Whereas there is good evidence for the effectiveness of Internet-based interventions (guided and unguided) for depression and other mental disorders [8, 25, 30], programs targeting chronic pain and depressive symptoms are rare and often poorly validated, with a lack of data on long-term effects [6, 31]. RCTs with high methodological standards that examine both the short-term and long-term effects of Internet-based interventions for people with chronic pain and comorbid depression in large samples are scarce.

In the present study, we aim to evaluate the feasibility, effectiveness, and acceptance of Lenio in an RCT. To do so, we intend to reach out to individuals who either have not (yet) sought conventional face-to-face therapy or who are seeking complementary treatment, thus narrowing the existing treatment gap. The advantages of Internet-based interventions such as Lenio are their low cost, anonymity, flexibility, and low-threshold access. To the best of our knowledge, no Internet-based program exists that concurrently treats patients with both chronic pain and comorbid depressive symptoms. To offer complete anonymity for participants, we developed an unguided Internet-based intervention. Offering direct support might increase effectiveness but could also prevent patients from participating due to fear or self-stigmatization.

To increase adherence, we developed a smartphone app to be used in combination with Lenio. In addition, e-mail reminders will remind participants to access and use the program. Moreover, we integrated a welcome module containing motivational interviewing techniques to increase participants’ motivation to work on psychological aspects of their chronic pain. Within the welcome module, participants will receive an individualized recommendation of the modules most effective for them. Personal goals can be set and easily adjusted at any time.

One possibility for the future is that Lenio could be used as an after-care tool (e.g., after inpatient treatment) to prevent relapse. In addition, due to limited resources (e.g., too few specialists) patients currently have long wait times before they can start therapy. Internet-based interventions could be used to bridge this waiting time and provide patients with psychoeducational information and psychotherapeutic interventions. When they later start therapy, the time gained can be used to address other aspects (e.g., interpersonal problems, comorbidities) of treatment. Furthermore, participation in an Internet-based intervention could facilitate motivation to engage in face-to-face treatment and thus prepare patients for conventional face-to-face therapy. To shed light on the question of which baseline characteristics affect the outcome (e.g., if no add-on effects emerged when Lenio is used in addition to standard treatment), a moderation analysis will be calculated.

Currently, CBT interventions are most effective for patients with chronic pain and for depressed patients [22]. Lenio is based on CBT and its third-wave techniques. We expect to add to the understanding of the feasibility, effectiveness, and acceptance of Internet-based interventions for people with chronic pain and depressive symptoms. We expect that Lenio will significantly reduce chronic pain impairment as well as depressive symptoms when compared to the control groups (waitlist control group and active control group). In addition, we expect that the effects will be maintained long term as assessed by the follow-up measurement 4 months after the baseline assessment.

## Trial status

Protocol version 03/22/2023. Second revision.

Any future changes to the study protocol will be recorded in separate amendment. See Table 4 for a detailed SPIRIT 2013 Checklist.

**Table 4 Tab4:** SPIRIT 2013 Checklist

Section/item	ItemNo	Description	Reported on page NO
**Administrative information**			
Title	1	Descriptive title identifying the study design, population, interventions, and, if applicable, trial acronym	1 (1)
Trial registration	2a	Trial identifier and registry name. If not yet registered, name of intended registry	2 (46)
	2b	All items from the World Health Organization Trial Registration Data Set	3
Protocol version	3	Date and version identifier	3 (table)
Funding	4	Sources and types of financial, material, and other support	3–4 (table)
Roles and responsibilities	5a	Names, affiliations, and roles of protocol contributors	1 (6) and 27 (524)
	5b	Name and contact information for the trial sponsor	3 (table)
	5c	Role of study sponsor and funders, if any, in study design; collection, management, analysis, and interpretation of data; writing of the report; and the decision to submit the report for publication, including whether they will have ultimate authority over any of these activities	3 (table)
	5d	Composition, roles, and responsibilities of the coordinating center, steering committee, endpoint adjudication committee, data management team, and other individuals or groups overseeing the trial, if applicable (see Item 21a for data monitoring committee)	23 (445)
**Introduction**			
Background and rationale	6a	Description of research question and justification for undertaking the trial, including a summary of relevant studies (published and unpublished) examining benefits and harms for each intervention	4 (57)
	6b	Explanation for choice of comparators	7 (144)
Objectives	7	Specific objectives or hypotheses	6 (128)
Trial design	8	Description of trial design including the type of trial (e.g., parallel-group, crossover, factorial, single group), allocation ratio, and framework (e.g., superiority, equivalence, noninferiority, exploratory)	6 (138)
**Methods: Participants, interventions, and outcomes**			
Study setting	9	Description of study settings (e.g., community clinic, academic hospital) and list of countries where data will be collected. Reference to where list of study sites can be obtained	7 (148)
Eligibility criteria	10	Inclusion and exclusion criteria for participants. If applicable, eligibility criteria for study centers and individuals who will perform the interventions (e.g., surgeons, psychotherapists)	10 (204)
Interventions	11a	Interventions for each group with sufficient detail to allow replication, including how and when they will be administered	11 (229)
	11b	Criteria for discontinuing or modifying allocated interventions for a given trial participant (e.g., drug dose change in response to harms, participant request, or improving/worsening disease)	7 (157) 23 (440)
	11c	Strategies to improve adherence to intervention protocols, and any procedures for monitoring adherence (e.g., drug tablet return, laboratory tests)	6 (122) 8 (171) 24 (465)
	11d	Relevant concomitant care and interventions that are permitted or prohibited during the trial	n/a
Outcomes	12	Primary, secondary, and other outcomes, including the specific measurement variable (e.g., systolic blood pressure), analysis metric (e.g., change from baseline, final value, time to event), method of aggregation (e.g., median, proportion), and time point for each outcome. Explanation of the clinical relevance of chosen efficacy and harm outcomes is strongly recommended	9 (table) 16 (277)
Participant timeline	13	Time schedule of enrolment, interventions (including any run-ins and washouts), assessments, and visits for participants. A schematic diagram is highly recommended (see Table 1)	7 (162) 8 (Table 1)
Sample size	14	Estimated number of participants needed to achieve study objectives and how it was determined, including clinical and statistical assumptions supporting any sample size calculations	10 (190)
Recruitment	15	Strategies for achieving adequate participant enrolment to reach target sample size	10 (193)
